**JUSTIFICATION**

Studies in countries like United States of America (USA), Australia, Canada and India have found metformin an effective and cheaper alternative to insulin. Genetic variations exist in the pathogenesis of diabetes mellitus as well as in the metabolism of metformin. Consequently results from one area may not be applicable in another. It is therefore important to do a Ghanaian study. There is no published data on the use of Metformin in pregnancy for glycaemic control in Ghanaians. The role of an effective but cheaper and more convenient to use medication in the control of any medical condition in a low – middle income country like Ghana cannot be overemphasized. Poor patient follow-up and monitoring in Ghana makes the use of drugs that do not require frequent monitoring, a preferred option at all times to those requiring frequent monitoring.

Insulin is less affordable and not readily available at all times. The need for refrigeration for effective insulin storage and use in developing countries is associated with difficulties. Unlike insulin, metformin does not require refrigeration for effective storage. Metformin is readily available and its oral administration is tolerable to many patients.

**LITERATURE REVIEW**

**Metformin**

Metformin is an oral hypoglycaemic agent which belongs to the biguanide class. Its history has been traced back to the use of a perennial herb, Galega officinalis. This herb has white, blue or purple flowers and grows over three feet high and is found in most temperate regions. Its common names include goat's rue, French lilac, Spanish sanfoin and false indigo. In folklore medicine, it is believed that G. officinalis was used to treat symptoms now ascribed to type 2 diabetes.^11^ G. officinalis continues to be cited for the treatment of diabetes in modern herbal pharmacopoeias.^11,12^ French physician Jean Sterne is credited with the first clinical trial of metformin (which he also called Glucophage) for the treatment of diabetes.^8, 11^

**CHEMISTRY/CLASSIFICATION**

The International Union of Pure and Applied Chemistry (IUPAC)’s systematic name for metformin is *N*,*N*-dimethylimidodicarbonimidic diamide**.** It is also referred to as 1,1-dimethylbiguanide**.** It is a basic compound with molecular mass 129.164 g/mol(free form) and 165.63g/mol (with HCl) .

[figure not shown]

[figure not shown]

www.chemistrydaily.com

PHARMACOKINETICS

Metformin is administered orally and absorbed mainly in the small intestine with a bioavailability of 40-60% at doses of 0.5 to 1.0 g. Absorption is complete in 6 hours after oral administration. Its bioavailability tends to decrease with increasing doses. This inverse relationship has led to the proposal of an active, saturable absorption process.^12^  Its half-life is 2 hours. It is stable and does not bind to plasma proteins.^13, 14^ Metformin decreases absorption of vitamin B12 and folic acid, although reported cases of megaloblastic anemia are rare. Cimetidine decreases the elimination of metformin in healthy subjects. ^15^  Metabolism is insignificant and excretion is primarily renal.

The renal clearance of metformin in men and non-pregnant women has been found to correlate with creatinine clearance but exceeded glomerular filtration rate, indicating active net tubular secretion. ^13^

A parallel increase in renal clearance of both metformin and creatinine in mid and late pregnancy has been demonstrated. While metformin renal clearance increased on average by 49% and 29% in mid and late pregnancy respectively, compared with postpartum, the changes in renal clearance of creatinine were 29% and 21% respectively. The changes in metformin renal clearance were not dependent on the subjects OCT2 genotype ^19^ though metformin is known to be a substrate for organic cation transporters (OCTs). ^16, 17, 18^ Renal OCT2 (encoded by *SLC22A2*) has been suggested to play a significant role in the pharmacokinetics of metformin. This is because a 30 to 60% change in metformin secretion clearance and renal clearance and up to a 74% change in its area under the concentration-time curve (AUC) in carriers of the variant *SLC22A2* alleles has been noted. ^16, 20, 21^ Metformin has been shown to cross the placenta readily. Umbilical cord concentrations at the time of delivery are at least half of the maternal concentrations and in some cases even exceed them. ^22, 23, 24^ A study by Hebert, et al found umbilical cord plasma concentration of metformin to vary from undetectable (<5 ng/ml) to 1263 ng/ml at the time of delivery ^19^.

Infant exposure following metformin administration during breast-feeding has been found to be low. The relative infant dose is reported to be between 0.11 to 1.08% of the mother’s weight- adjusted dose ^22, 23, 24^.

**PHARMACODYNAMICS**

Metformin is an effective oral hypoglycemic agent that improves insulin sensitivity. ^25^ Metformin has a greater postprandial effect than the sulfonylureas and insulin, and is therefore more useful in patients with postprandial hyperglycaemia. The sulfonylureas and insulin on the other hand are more effective in managing poorly controlled fasting hyperglycaemia. ^15^
 Metformin reduces free testosterone levels and increased sex hormone-binding globulin (SHBG). It improves menstrual irregularities leading to spontaneous ovulation and improved ovarian response to conventional ovulation induction therapies. ^25,^

The introduction of metformin for the treatment of polycystic ovary syndrome (PCOS) provided evidence supporting its use in pregnant women. ^28^ Metformin has been recommended for use during pregnancy for the treatment of gestational as well as preexisting diabetes mellitus. ^29^

The exact mechanism of action of Metformin is not fully understood despite its wide clinical usage. Metformin does not stimulate insulin secretion.
It exerts its hypoglycaemic effect via metabolic activities at several sites of action, including liver, adipocytes, intestine, and muscle cells. The activities in these sites of action (Biophases) include:

1) Decreased hepatic glucose output due to decreased hepatic gluconeogenesis and increased glycogenesis and lipogenesis; ^30^

2) Reduced rate of intestinal glucose absorption; ^31^ and

3) Increased glucose uptake by muscle cells and adipocytes ^32^

The relative contribution of these individual sites of action to the overall glucose-lowering effect is unknown and a subject of continuing research in animal models^33^. This is because the dose-response relationship of the metabolic effects in individual organs and tissues is obscured by the multifactorial mechanism of metformin and the complex nature of glucose homeostasis in-vivo ^33^

**METHODOLOGY**

STUDY DESIGN

The study design is a prospective, randomized comparative study. Participants will be randomly assigned into one of the two treatment groups. For a set of four (4) patients seen at the clinic for the first time, they will be made to ballot by picking randomly one paper with an inscription each from an opaque envelope. This assigned participants to one of the two treatment groups – insulin and metformin. This will be repeated till the sample size is attained. The sequence of picking will be in the order in which they reported to the clinic; “first to report, first to pick”**.**  The participants in each group will be matched for age, parity, gestational age, pre-treatment weight and pre-treatment glycaemic profile.

Treatment will be administered to each according to the study treatment protocols. Subjects in both groups will follow the routine antenatal schedule and their blood glucose levels will also be checked and recorded during these visits according to existing protocols. For in-patients a similar routine will be followed.

STUDY AREA

The study will be conducted at the Maternity Unit and the Diabetes Centre of Korle Bu Teaching Hospital. It will involve both in- patients and out-patients in these units.

STUDY SUBJECTS

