**ABSTRACT**

**Background:** Diabetes mellitus is an important complication of pregnancy with adverse effects on both mother and fetus. Poor control of pre-gestational diabetes during the period of organogenesis increases the risk of major congenital malformations. While insulin is effective in controlling high blood glucose levels, otherwise resistant to diet and exercise management, several factors hinder its use. Metformin has been found to be a convenient, cheap, effective and safe hypoglycaemic agent in some countries and it is likely to do same among Ghanaian women.

**Aim:** The main aim of this study is to determine if metformin monotherapy or metformin in combination with insulin is equally effective at attaining and maintaining glycaemic targets compared to insulin monotherapy in the management of gestational diabetes mellitus and type 2 pre-gestational diabetes mellitus in Ghanaians.

**Methodology:**  A prospective randomized comparative study is proposed. Patient selection and randomization will be done using balloting with opaque envelopes. Participants will be followed through their index pregnancy with 2-weekly glycaemic profile monitoring and maternal weight gain. Babies delivered will be followed till the sixth week post-delivery measuring birth weight, incidence of birth trauma and neonatal intensive care unit (NICU) admission rates. Both laboratory and clinical data will be recorded and analyzed.

**Expected outcome:** It is expected that pregnant diabetics treated with metformin will have a lower 2HPG levels at the end of the study than those treated with insulin. The 2-hour post prandial glucose (2HPG) level is the measure selected to estimate the effectiveness of glycaemic control.

In addition NICU admissions are expected to be higher in the insulin group than metformin group.

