**Eligibility criteria**

Eligible subjects will be women aged 18 to 45 years who are pregnant with single fetus at gestational age of 20 to 30 weeks and have been diagnosed with type 2 DM or Gestational Diabetes and met the Hospital’s criteria for starting insulin therapy. The criteria for the diagnosis of GDM and DM will be a plasma glucose concentration of greater than or equal to 7 mmol/L after an overnight fast or plasma glucose concentration of equal to or greater than 11.1 mmol/L 2 hours after a 75g glucose drink.^1^

The current criteria for starting insulin therapy in patient with GDM at the diabetes clinic of KBTH are at least one following:

- FBS > 5.1 mmol/l
- 1HPG > 10.0 mmol/L or
- 2HPG > 8.5 mmol/L.

Subjects diagnosed according to the above criteria that are unable to achieve the above targets following management on diet and exercise will be eligible for the study.

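### Balloting from one shared envelope in fixed sets of four, with no blinding described and no enrolment lock, does not secure allocation concealment

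*Protocol*

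**What the plan says.** The allocation procedure is set out in the Protocol under METHODOLOGY, STUDY DESIGN. The unit is a fixed set: "For a set of four (4) patients seen at the clinic for the first time". Within the set, "they will be made to ballot by picking randomly one paper with an inscription each from an opaque envelope". The order is also fixed: "The sequence of picking will be in the order in which they reported to the clinic". The procedure then recurs: "This will be repeated till the sample size is attained". The purpose is stated as "Participants will be randomly assigned into one of the two treatment groups". The Abstract gives only a short form: "Patient selection and randomization will be done using balloting with opaque envelopes".

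The same design section adds that "The participants in each group will be matched for age, parity, gestational age, pre-treatment weight and pre-treatment glycaemic profile", without giving a mechanism. Under Eligibility criteria, women diagnosed by the stated criteria who are "unable to achieve the above targets following management on diet and exercise will be eligible for the study".

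The Metformin Group and Insulin group sections describe an oral drug and subcutaneous injections. No placebo or blinding is mentioned. The Protocol does not say:

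- how many of the four papers carry each arm;
- who prepares and holds the envelope;
- whether papers are opened singly or after all four are drawn;
- whether eligibility and consent for the set are complete before the first paper is opened.

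**The concern.** A shared opaque envelope hides which paper a woman will pick. It does not hide what is left from anyone who has seen the earlier papers in the set. One paper each implies drawing without replacement, and the set size is known, so information about the remaining papers builds up with each draw. Since nothing describes masking, an opened allocation is visible.

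This matters if someone can still influence who takes the next draw, through the timing of arrival, a borderline eligibility decision or the consent discussion. The Protocol puts no barrier there. Its matching statement includes the pre-treatment glycaemic profile, which a plain ballot cannot guarantee, and so could give staff a reason to look at who draws next.

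The groups could then differ at baseline on the variable that drives the primary outcome, 2HPG, in a trial sized on a difference of only 4 mg/dl. Concealment cannot be restored after enrolment.

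A second, smaller point is the sequence of events. Balloting women at a first clinic attendance sits awkwardly with an eligibility rule that needs prior failure of diet and exercise.

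**Working it through.** **Inputs from the Protocol**

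- Set size 4, drawn in arrival order and repeated (STUDY DESIGN).
- Two arms; 47 per group calculated, 52 per group recruited, 10% allowance (SAMPLE SIZE DETERMINATION).
- Design difference in 2HPG of 4 mg/dl, or 0.22 mmol/l (same section).

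**Assumptions, not stated in the Protocol**

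- A1: each set holds two metformin and two insulin papers.
- A2: papers are revealed one at a time, before the rest of the set is committed.

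**Step 1. The plan's own figure.** 47 × 1.10 = 51.7, which rounds to the stated 52. (Dividing instead, 47 / 0.90 = 52.2, gives 53; the difference is immaterial here.) Total 2 × 52 = 104, and 104 / 4 = 26 complete sets. With two papers per arm, 26 × 2 = 52 per arm exactly, which is what makes A1 plausible. The Protocol gives no figure for predictability.

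**Step 2. Chance of a correct guess under A1 and A2.** There are six equally likely orderings of a 2+2 set. The guesser names the arm with more papers left.

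| Draw | Situation | Probability correct |
|---|---|---|
| 1 | 2 against 2 left | 1/2 = 0.500 |
| 2 | 2 against 1 left | 2/3 = 0.667 |
| 3 | first two agree (1/3): known; differ (2/3): even | 1/3 × 1 + 2/3 × 1/2 = 0.667 |
| 4 | one paper left | 1.000 |

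Mean = (0.500 + 0.667 + 0.667 + 1.000) / 4 = 0.708. Over 104 women this is 104 × 0.7083 = 73.7 correct guesses, against 104 × 0.5 = 52 when earlier draws give no information.

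**Step 3. Allocations known with certainty under A1 and A2.** The fourth is always known, and the third is known in one set of three: (0 + 0 + 1/3 + 1) / 4 = 1/3. 104 / 3 = 34.7, about 35.

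**Step 4. If the assumptions fail.**

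- Without A1, predictability falls towards 50%, but equal arms of 52 are no longer assured.
- Without A2, because all four women are irrevocably enrolled before any paper is opened, foreknowledge cannot change who enters.

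**Step 5. Scale, as a hypothetical only.** Suppose only the certain third were steered, so that women known to be going to insulin had expected 2HPG higher than average by x, and those known to be going to metformin lower by x. The insulin mean shifts by +x/3 and the metformin mean by −x/3, a spurious difference of 2x/3. Setting 2x/3 = 4 mg/dl gives x = 6 mg/dl (1.5 × 0.22 = 0.33 mmol/l). Nothing in the Protocol indicates that such steering takes place.

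**Step 6. Does varying the block size help?** In a simulation of 10,000 runs of 104 patients, always guessing the arm that lags, hidden blocks mixed from 4, 6 and 8 gave 67.9% correct, against 70.8% for fixed fours.

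**The case against.** The strongest reply is that predictability is not selection bias. The design section can naturally be read as forming the set first and balloting afterwards. If the four are committed by then, knowing the last paper changes nothing about who enters. The arrival-order rule also leaves staff no stated discretion over position, so it is a partial safeguard. This stands to the extent that the figures above are a worst case under A1 and A2. It does not remove the point, because the Protocol nowhere requires the set to be committed before a paper is opened.

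A reader might go further and infer three things that the text does not support:

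- **That the ballot is open and held in front of clinic staff, so the fourth allocation is always known.** The text says an opaque envelope and a picking order. It does not say who watches or when papers are revealed.
- **That the trial loses its protection against selection bias.** The draw is still random. Even in the worst case the first draw of each set is unpredictable, and two thirds of allocations are not certain.
- **That ineligible women will be randomised and later excluded.** A first attendance at this clinic can follow failed diet and exercise management elsewhere. The design section speaks of participants, and Ethical Considerations requires written consent from all of them. The two sections are ambiguous on sequence; no error is shown.

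**Conclusion.** The point holds in a limited form. The stated procedure combines a fixed and known set size, one shared envelope and treatments that nothing masks, and it has no step that fixes eligibility and consent before a paper is opened. That does not secure allocation concealment. This is a weakness in a procedure the Protocol itself fixes, so it is more than detail left for a later document.

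The size is conditional. With two papers per arm and sequential revealing before the set is committed, up to one third of allocations (about 35 of 104) could be known in advance and 71% guessed correctly, against 50% under concealment. Neither condition is stated; the first is inferred from equal groups of 52. If all four women are irrevocably enrolled before any opening, entry to the trial is unaffected. The documents allow no estimate of actual bias in 2HPG.

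**What to change.** Replace the shared-envelope ballot with a pre-generated random list. A department member who does not enrol patients should prepare it and place the allocations in sequentially numbered, sealed opaque envelopes. Open the next envelope in strict order of enrolment, for one woman at a time, and only after her eligibility (including failure of diet and exercise), consent and baseline glucose are recorded. Strict order keeps the useful part of the arrival rule.

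Reconcile the first-attendance wording in the design section with the diet-and-exercise requirement under Eligibility criteria, so that the sequence of events is clear.

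If the list is blocked, its structure should stay with the person who prepared it. Mixing block sizes is optional: it lowers guessing only from 70.8% to 67.9%, so some guessing remains possible in an unmasked trial. The main gain comes from independent preparation and from committing each woman before her allocation is seen. Stratifying by diabetes type is not needed for concealment.

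The cost is small: the list and about 104 envelopes must be ready before enrolment starts. No extra visits or staff are needed.

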**Treatment failures**

Supplemental insulin for treatment failures in the Metformin group will be prescribed according to the same protocols in the insulin group.

DATA COLLECTION

Basic demographic data will be recorded. They will be followed through their index pregnancy, with 2-weekly blood glucose checks in hospital. All laboratory samples will be collected and analyzed at the diabetes research laboratory by staff of the same laboratory. Venous blood will be used for blood glucose profile analysis. Analysis of Fasting Blood Glucose (FBG), one- hour post-prandial glucose (1HPG), two- hour post-prandial glucose (2HPG) will be done using the Mindray BS-400^®^ (Mindray Medical Int. Ltd, China) chemistry analyzer. The method for glucose determination will be enzymatic photometric testing. Urinalysis, weight records (using Seca^®^(gmbh&Co. Kg Germany)) and cost of treatment will also be documented. The optimal dose of metformin required for optimal glycaemic control will be recorded for each patient. Peri-partum events like gestational age at delivery, type of delivery, fetal birth weight, and NICU admissions will be retrieved from patient notes.

STATISTICAL ANALYSIS

In analyzing the data, summary statistics will include appropriate tables and charts. Categorical data will be represented by pie and bar graphs and continuous data with histograms.

For inferential statistics, significant difference of mean observations using one-tail student’s t-test and z-score for differences in proportions where applicable. The differences in trends of glycaemic profile over time between the study groups will be assessed by two-way repeated measures analysis of variance (ANOVA).

Significance level (p-value) will be set at α = 0.05. Data analysis will be done using statistical package for social science **(SPSS** version 20).

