**EXPECTED OUTCOME**

It is expected that pregnant diabetics treated with metformin will have a lower 2HPG levels at the end of the study than those treated with insulin. The primary outcome is the difference in the 2HPG level between the metformin and insulin group. The rationale for selecting 2HPG is that by its mechanism of action, metformin is expected to have a more significant blood glucose lowering effect in the postprandial period than the fasting period. Hyperglycaemia in the prandial period is related to insufficient suppression of hepatic glucose output, poor insulin release and ineffective glucose disposal in target tissues (especially muscles) by insulin (insulin resistance) and metformin affect all these Biophases.^30-32^

Secondary outcomes to be measured include glycaemic profile (measured by FBG, 1HPG, and HB1AC), fetal birth weight, maternal weight gain and caesarean section rate which are expected to be lower in the metformin group, number of NICU admission which is expected to be higher in the insulin group. If found to be effective it may form the basis for developing a policy for Diabetes Mellitus care in pregnancy at primary and secondary level of healthcare instead of the current tertiary level of care.

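### The protocol promises matched groups that its ballot cannot produce, and its t-test for means names no covariate although pre-treatment 2HPG is available

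*Protocol*

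**What the plan says.** **Allocation (Protocol, Methodology, Study Design).** For each set of four new patients, "they will be made to ballot by picking randomly one paper with an inscription each from an opaque envelope". The order is fixed by arrival: "The sequence of picking will be in the order in which they reported to the clinic". No baseline variable enters the draw. The same paragraph then says: "The participants in each group will be matched for age, parity, gestational age, pre-treatment weight and pre-treatment glycaemic profile".

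**Sample size (Protocol, Sample Size Determination).** A formula for two independent means gives 47 per group for a 4 mg/dl difference in 2HPG at 34 weeks, with 80% power and α = 0.05. This is raised to 52 for non-response.

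**Analysis (Protocol, Statistical Analysis).** Means and proportions are compared as follows: "significant difference of mean observations using one-tail student’s t-test and z-score for differences in proportions where applicable". A two-way repeated measures ANOVA is assigned to trends in the glycaemic profile over time.

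**Primary outcome (Protocol, Expected Outcome).** "The primary outcome is the difference in the 2HPG level between the metformin and insulin group". It is not tied to a named test.

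**Population (Protocol, Eligibility criteria).** Women at 20 to 30 weeks who "have been diagnosed with type 2 DM or Gestational Diabetes and met" the hospital's criteria for insulin, so both diabetes types enter.

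**The concern.** The matching sentence can be read in two ways, and neither fits the rest of the plan.

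- Read literally, it could be met only by selecting, redrawing or dropping women once their baseline values are known. That would undermine the ballot, and the unpaired formula and test would no longer reflect the design.
- Read as an expectation that the groups will be alike, it promises a balance that about 50 women per arm does not reliably give.

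The analysis raises a second, smaller point. The protocol names pre-treatment glucose, weight and gestational age as characteristics on which the groups should be alike, but gives them no role when means are compared. At stake is precision on the primary outcome. For maternal weight gain, women entering anywhere between 20 and 30 weeks have up to 10 weeks' difference in the time available to gain weight, which adds noise.

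**Working it through.** **1. The plan's own figure.** No SD for 2HPG is stated, so 47 per group cannot be reproduced forward. Solving n = 2·SD²·(z_α + z_β)²/δ² backwards with n = 47 and δ = 4 mg/dl gives SD = 4·√(47/2)/(z_α + z_β):

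- one-sided: 4 × 4.848/2.486 = 7.8 mg/dl
- two-sided: 4 × 4.848/2.802 = 6.9 mg/dl

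The power statement gives no sidedness; the Statistical Analysis section is one-tailed. Both are carried below. The 52 is 47 × 1.10 = 51.7, rounded up.

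**2. What the ballot delivers.** Even if each set of four holds two papers per arm (not stated), the draw balances numbers only. With 52 per arm, the chance difference in any standardised baseline mean has SD √(2/52) = 0.196, so its 95% range is ±0.38 SD. For one variable, P(|difference| > 0.2 SD) = 0.308. For five variables, treated as independent (an assumption), P(at least one > 0.2 SD) = 1 − (1 − 0.308)⁵ = 0.84. A simulation of 2:2 ballots in sets of four gave 0.83.

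**3. What such an imbalance does to one unadjusted result.** A 0.2 SD difference in baseline 2HPG shifts the expected final difference by r × 0.2 × SD, where r is the baseline to 34-week correlation.

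- r = 0.3, SD 6.9: 0.4 mg/dl, or 10% of the 4 mg/dl target
- r = 0.7, SD 7.8: 1.1 mg/dl, or 27% of the target

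The direction is random, and the standard error of the t-test already allows for this variation.

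**4. Gain from adjusting for baseline 2HPG.** ANCOVA multiplies the residual variance by 1 − r². Power at 47 per arm is therefore Φ[(z_α + z_β)/√(1 − r²) − z_α]. The protocol gives no r, so a range is assumed.

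| r (assumed) | 1 − r² | Power, one-sided | Power, two-sided | Unadjusted n per arm worth the same, 47/(1 − r²) |
|---|---|---|---|---|
| 0.1 | 0.99 | 80.3% | 80.4% | 48 |
| 0.2 | 0.96 | 81.4% | 81.6% | 49 |
| 0.3 | 0.91 | 83.2% | 83.6% | 52 |
| 0.5 | 0.75 | 89.0% | 89.9% | 63 |
| 0.7 | 0.51 | 96.7% | 97.5% | 93 |

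Sidedness hardly matters; r decides the size. These figures take the stated 80% base power as given.

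**The case against.** The strongest reply is that the analysis half asks for an improvement and identifies no error. Under intact randomisation the unadjusted t-test keeps its type I error rate, and covariate lists are often left to a statistical analysis plan, which may exist. This stands: the loss is precision only. A reader might infer from the chance-imbalance figures that the planned comparison is biased or invalid; it is not.

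A reader might also infer that the plan throws baseline glucose away. The documents do not support that. The repeated measures ANOVA covers the glycaemic profile, of which 2HPG is part, and the text does not say whether the pre-treatment value is one of its time points. Nor is the primary outcome tied to either method. But that ANOVA is assigned to trends over time, whereas the trial is powered on a difference in means at 34 weeks, the kind of comparison for which the t-test is named.

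The gain may also be small. Both arms are titrated to fixed glucose targets, and 34 weeks falls 4 to 14 weeks after entry, so the correlation with baseline could be weak. At 0.1 to 0.2 there is almost nothing to gain. This stands too, and is why the range starts there.

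Finally, matched may mean no more than expected to be comparable. That is possible, but the text does not say it, and the sentence describes study design, which is not detail to be left to an analysis plan.

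**Conclusion.** The contradiction over matching is firm and rests on the text alone: the only allocation method described ignores all five variables said to be matched, and the sample size and test assume independent groups. A stronger reading, that women will in fact be redrawn or excluded to force balance, is not supported. No such step is described; the risk is that the sentence invites one.

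The analysis point is secondary and concerns efficiency. Adjusting for pre-treatment 2HPG would raise 80% power to somewhere between 80% and 98% over correlations of 0.1 to 0.7. That rests on an assumed correlation, a linear relation with baseline, and the stated 80% being right for 47 per arm. Both points are worth correcting because the correction is nearly free.

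**What to change.** 1. In Study Design, delete the matching sentence or replace it with: baseline characteristics will be compared descriptively. Add that no woman is redrawn or dropped to achieve balance. If balance on particular factors is wanted by design, describe an actual stratification scheme instead.
2. In Statistical Analysis, name ANCOVA for 2HPG at 34 weeks, with treatment and pre-treatment 2HPG, plus gestational age at entry and diabetes type (gestational or type 2) as pre-specified covariates.
3. Analyse maternal weight gain with adjustment for pre-treatment weight and gestational age at entry.
4. State whether the repeated measures ANOVA includes the pre-treatment value as a time point.

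The cost is wording and a covariate list fixed in advance. Pre-treatment glucose, weight and gestational age are already named in the protocol. Diabetes type is not among the listed data items but is known from eligibility, so it only needs a field on the record form. No extra visits, samples or women are needed.
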